### The Participants‐Inclusion and Exclusion Criteria

2.2

After a median of 12‐month DAPT run‐in phase after DES implantation, a total of 8250 eligible patients recruited from ≥ 100 cardiology centers across China and randomized to continue a prolonged 12‐month DAPT treatment (75 mg clopidogrel plus 75–150 mg aspirin daily) or a monomer treatment (75–150 mg aspirin daily) until study completion. The enrolled subjects will have angiographically confirmed MVD with stenosis of ≥50% in more than two major epicardial coronary arteries and stenosis in the left main coronary artery ≤30% by visual assessment. Additional details of the inclusion and exclusion criteria are shown in Table 1.

**Table 1 clc70049-tbl-0001:** Inclusion/exclusion criteria.

Inclusion	Exclusion
Aged 18–75 years old (inclusive). Patients with MVD who underwent DES implantation for 12 months. Patients have been treated with aspirin and can tolerate aspirin at doses of 75–150 mg/day as maintenance therapy during the study period. Patients have signed informed consent.	Planned to use of ADP receptor blockers (eg, clopidogrel, ticagrelor, and ticlopidine), dipyridamole, or cilostazol. Contraindication to ADP receptor blockers or aspirin. Anticoagulants were planned to be used during the study period. Planned major cardiac or noncardiac surgery during the study period. Concomitant oral or intravenous therapy with CYP2C19 medium or strong inhibitors. Known severe liver disease (ALT/AST is three times above normal). Subjects with renal failure who required or anticipated dialysis during the study period. Platelet count < 50 × 10^9^/L. Patients with a. A history of intracranial bleeding or ischemic stroke at any time; b. A central nervous system tumor or intracranial vascular abnormality (e.g., aneurysm, arteriovenous malformation) at any time; c. Intracranial or spinal cord surgery within five years. Pregnancy or lactation or planned to be pregnant during the study period. Life expectancy < 1 year. In the investigator's opinion, any condition would make it unsafe or unsuitable for the patient to participate in this study (e.g., active malignancy other than squamous or basal cell skin cancer). Concern for the inability of the patient to comply with study procedures and/or follow‐up (e.g., alcohol or drug abuse). Participation in another clinical study and did not reach the major endpoint. Involvement in the planning and/or conduct of the study.

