### Randomization and Treatment

2.3

After assessment for study eligibility requirements, patients will be assigned on a 1:1 basis to either the treatment group or the control group using a completely random method. Randomization will be conducted by a central computer network system. All eligible patients enrolled will receive 75–150 mg aspirin daily, and the treatment group will be recommended to take 75 mg clopidogrel daily for an additional 12 months from randomization. The subjects will receive experimental drug (the dose for 6 months, including the window period) at the research centers and their 6‐month follow‐up. As the study population is stable, no loading dose will be administered. Researchers may adjust the dose and regimen for antiplatelet medicines when adverse events occur in subjects. Other concomitant medications must be taken under the guidance. Any adjustment and distribution of study drugs should be recorded on the CRF form.

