### Follow‐Up

2.5

After randomization, participants will receive the assigned experimental drug treatment according to their group and have their treatment adherence and concomitant medication assessed at 1, 3, 6, 9, and 12 months of follow‐up. The experimental drug will be discontinued 12 months post‐enrollment. Participants may stop treatment at any time, and the experimental drug will also be discontinued if the researchers believe continued treatment poses potential risks. Then, after discontinuing the experimental drug 12 months post‐enrollment, subjects will continue to complete a 36‐month visit and the study close‐out visit (SVC) (12 months after the enrollment of the last patient). We will follow up on all participants’ potential endpoints and adverse events until death or the end of the follow‐up period.

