### Sample Size Calculation

2.6

Based on data extracted from the PEGASUS‐TIMI 54 study, the expected annual rate of MACCEs is estimated to be 5% in the control arm [19]. It is anticipated that prolonged DAPT treatment in patients with MVD will reduce the target relative risk by 20% (i.e., the hazard ratio [treatment/control] is equal to 0.8) and the per‐year event rate by approximately 4% for the primary endpoint in those populations [20, 21]. Moreover, a two‐sided test is set at the 5% significance level, and 80% power is designed to reject the null hypothesis. The enrollment duration is estimated to be 24 months, and the follow‐up time is at least 12 months (with an expected median follow‐up time of 24 months). The enrollment progress in both groups was consistent, and eligible patients will be randomized on a 1:1 basis according to the protocol. Considering a 5% dropout rate and an expected noncompliance (switching groups) rate in those groups will be 3%. Therefore, the DAPT‐MVD trial is required to enroll at least 8250 subjects (4125 in each arm).

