### Statistical Considerations

2.7

All potential endpoints will be adjudicated by the CEC and included in the efficacy analysis in the intention‐to‐treat (ITT) set, and a cross table of judgment results for the events will be listed. Subjects may develop more than one event during the study. For the composite endpoint, only the first event that occurs will be included in the time‐to‐event endpoint analysis. Unless otherwise specified, all statistical tests will be two‐sided and conducted at a 5% significance level. The detailed descriptions are summarized in Supporting Information S1: Appendix 1.

The primary endpoint will be the time from randomization to the first occurrence of its component. Initially, the Kaplan–Meier method will be employed to estimate the cumulative incidence of the primary endpoint and a log‐rank test will be conducted to compare survival curves between the treatment arms. Furthermore, a Cox proportional hazards model will be utilized to compare the hazard of having a primary outcome between the prolonged DAPT arm and control arm, providing a hazard ratio along with a 2‐sided 95% confidence interval (CI) to measure the treatment difference. In addition, the win‐ratio method for the hierarchical composite outcome will be performed as a supplementary analysis (Supporting Information S1: Appendix 1) [22]. All secondary time‐to‐event endpoints will be analyzed similarly as for the primary endpoint.

All safety analyzes will be based on the safety set. Descriptive statistical methods will be used to summarize the study drug exposure, the causes and times of study drug discontinuation, concomitant drugs, protocol deviations, clinical laboratory data, vital signs, and physical examination results in each treatment group. Patients not having suffered any bleeding event in the given category will be censored at the earliest of 7 days after the last dose of the study drug, death, last contact, or withdrawal of consent.

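### The only stated bleeding rule censors 7 days after the last dose of study drug: the control arm has no clear anchor, censoring may be informative, and the window can be far shorter than that for MACCE

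*Protocol article*

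**What the plan says.** Section 2.4 names two safety endpoints, BARC type 2–5 and BARC type 3–5 bleeding. Section 2.7 places safety analyses in the safety set and states a single rule for bleeding follow-up: patients without an event are "censored at the earliest of 7 days after the last dose of the study drug, death, last contact, or withdrawal of consent". It does not say what the study drug is for a control patient.

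On treatment, section 2.3 gives aspirin to everyone and adds that "the treatment group will be recommended to take 75 mg clopidogrel daily for an additional 12 months from randomization". Section 2.2 ends its description of the control regimen with "mg aspirin daily) until study completion", whereas the legend to Figure 1 puts control aspirin inside a 12-month period. Section 2.5 ends the experimental drug at 12 months, says "Participants may stop treatment at any time", and has it discontinued when the researchers see potential risk in continuing. The same section follows endpoints and adverse events to death or the end of follow-up.

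MACCE is analysed by intention to treat as time from randomisation (section 2.7). NACE, a secondary endpoint made up of MACCE plus BARC 2–5 bleeding (section 2.4), is to be analysed in the same way as the primary endpoint.

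**The concern.** Censoring shortly after the last dose fits a placebo-controlled trial, where each arm has a matched product to stop. Here the arms differ in whether there is an added drug at all. Following the rule as printed raises three problems:

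- The date at which a control patient leaves the bleeding analysis depends on a term the article leaves open.
- In the DAPT arm, that date depends on a decision that may itself reflect bleeding risk. The risk set is then no longer the randomised one.
- Bleeding may be counted over a much shorter period than MACCE, and the same BARC 2–5 bleed can count in NACE but not in the bleeding endpoint.

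The introduction and discussion make weighing ischaemic benefit against bleeding a central aim. A rule that can understate harm errs in the unfavourable direction for a safety endpoint.

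**Working it through.** **1. The plan's own figure.** The article gives no power or follow-up figure for bleeding. The sample size can be checked, and it confirms the MACCE follow-up pattern used below.

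- Inputs from section 2.6: "the expected annual rate of MACCEs is estimated to be 5% in the control arm"; "the hazard ratio [treatment/control] is equal to 0.8"; two-sided 5% level, 80% power; 24-month accrual; 12-month minimum follow-up; 5% dropout; 3% switching.
- Events (Schoenfeld): 4 × (1.96 + 0.8416)² / (ln 0.8)² = 631.
- Event probability with uniform accrual A = 2 years and minimum follow-up F = 1 year: p = 1 − [exp(−λF) − exp(−λ(F + A))] / (λA). For λ = 0.05, p = 9.48%; for λ = 0.04, p = 7.66%; mean 8.57%.
- N = 631 / 0.0857 ≈ 7362; divided by 0.95 gives 7750; divided by 0.97² gives 8237, against 8250 stated. The article does not say how switching was applied, so this is one route that fits. The sample size is not in dispute.

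**2. What the rule means in each arm.** For DAPT patients, if study drug means the 12-month regimen, the cap is 12 months + 7 days = 12 + 7/30.44 = 12.2 months. For controls there are three readings:

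| Study drug in the control arm | Control bleeding window |
|---|---|
| Clopidogrel only | No last dose, so the rule has no anchor |
| Aspirin to study completion (section 2.2) | To close-out, on average about 24–33 months |
| Assigned regimen within 12 months (Figure 1 legend) | At most 12.2 months, as in the DAPT arm |

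**3. Bleeding window against MACCE window.** Mean MACCE follow-up under uniform accrual is 12 + (accrual in months)/2.

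- As planned: 12 + 24/2 = 24 months, in line with the expected median of 24 in section 2.6. Share covered: 12.2/24 = 51%.
- With the 18-month extension in section 5 (24 + 18 = 42 months; uniform accrual assumed): 12 + 42/2 = 33 months. Share covered: 12.2/33 = 37%.
- Early stopping shortens this further. If a fraction q of DAPT patients stops uniformly over year 1 (assumed), the mean window is (1 − q) × 12.23 + q × 6.23 months: 11.9 at q = 5% and 10.4 at q = 30%.

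**4. Informative censoring.** This is an illustration and every input is assumed: control bleeding 1.5% per year; on-drug rate ratio 1.6; gamma frailty with variance 1 or 2; 10–30% of DAPT patients stopping in year 1; no early censoring of controls.

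| Stopping in the DAPT arm | Frailty variance 1 | Frailty variance 2 |
|---|---|---|
| Unrelated to bleeding risk, 7-day censoring | about 1.6 | about 1.6 |
| Driven by the same frailty, 7-day censoring | 1.52 to 1.37 | 1.46 to 1.25 |
| Driven by the same frailty, as randomised to 12 months | 1.54 to 1.43 | 1.51 to 1.41 |

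The as-randomised ratio is also below 1.6, because stoppers return to the control rate. That is dilution of a valid treatment-policy effect, not selective loss from the risk set. A BARC 2–5 bleed that itself leads to stopping is counted under either approach. The bias comes from stopping for minor bleeding or perceived risk before a qualifying bleed.

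**5. Do unequal maximum windows alone distort the hazard ratio?** Assume bleeding hazards of 0.02 (control) and 0.036 (DAPT) per year, a true ratio of 1.8. Crude proportions mislead: DAPT to 1.02 years gives 1 − exp(−0.036 × 1.02) = 3.6%. Control to close-out gives 3.9% (24-month accrual) or 5.3% (42-month), from the formula in step 1 with λ = 0.02. In simulated trials with 4125 patients per arm on these inputs, however, the Cox hazard ratio stayed at about 1.8 for both accrual periods. After the last DAPT patient is censored, the risk set holds only controls and contributes nothing to the comparison.

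**The case against.** The strongest reply has four parts.

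- **A symmetric reading exists.** The Figure 1 legend gives both arms a 12-month regimen. Section 2.5 speaks of assigned treatment by group, and section 2.7 summarises drug exposure and discontinuation for each group. This stands: it is one of three readings, and the others cannot be excluded until the statements are reconciled. Controls may also stop treatment, so early stopping is not confined to the DAPT arm.
- **On-treatment bleeding analysis is legitimate.** This stands too. The weakness is that it is the only bleeding rule stated and has no clear control anchor. An appendix or SAP that is not shown may define the term or add an as-randomised analysis.
- **NACE already weighs benefit and harm over one window.** Correct. A reader might infer that the two cannot be compared over the same period at all; the NACE analysis rules that out. It does not give bleeding alone over that period, and it does not cover BARC 3–5 separately.
- **The size of the bias is assumed.** Also correct. The documents give neither a bleeding rate nor a rate of stopping clopidogrel for bleeding concern.

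A reader might also infer that following controls to close-out while DAPT bleeding stops near 12 months would hide an excess of bleeding. Step 5 shows that this is true of crude proportions only. A censoring rule implies a time-to-event comparison, and there unequal maximum windows alone do no harm.

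**Conclusion.** The point holds in limited form: should-fix, moderate confidence.

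Two parts follow directly from the text. First, the control-arm censoring anchor is unresolved, because sections 2.2, 2.3 and 2.5 and the Figure 1 legend do not agree on what a control patient's study drug is or when it ends. Second, if study drug means the 12-month regimen, bleeding is counted for at most about 12.2 months, which is about 51% of mean MACCE follow-up as planned and about 37% with 42-month uniform accrual. A bleed more than 7 days off drug then enters NACE but not the bleeding endpoint.

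A third part is inference. Because the added drug may be stopped for perceived risk in an open-label trial, censoring can be informative even with equal maximum windows, and the likely direction is to understate the bleeding hazard ratio. The documents do not fix its size. It is zero if stopping is unrelated to bleeding risk, and smaller if controls stop aspirin for similar reasons. The documents do not support a claim that the bleeding hazard ratio is certainly biased or that the arms certainly have different windows.

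**What to change.** 1. Reconcile the statements on the duration of control aspirin (section 2.2 and the Figure 1 legend) with sections 2.3 and 2.5, and define study drug and last dose for each arm.
2. Make the main analysis of BARC 2–5 and BARC 3–5 an as-randomised analysis of all randomised patients, from randomisation to a common fixed time of month 12 plus 7 days in both arms, regardless of adherence.
3. Add the same as-randomised analysis over the MACCE follow-up, so that bleeding can be set beside MACCE and NACE over one period.
4. Keep the 7-day on-treatment analysis as a sensitivity analysis, with the censoring anchor defined in each arm. Where windows differ by arm, do not report crude proportions.

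The cost is some SAP wording and one or two extra runs. No new data are needed, since section 2.5 already follows endpoints and adverse events to the end of follow-up. The price is some dilution of the bleeding effect by early stoppers, for which the retained on-treatment analysis gives a comparison. If the SAP already contains items 2 to 4, only item 1 remains.

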Covariate adjustment analysis aims to control for possible imbalances in the covariates, as listed in Table 2. The Cox model will be used for the covariate‐adjusted analysis, and the adjusted hazard ratio with its 95%CI will be estimated. In addition, subgroup analysis will be performed to assess the homogeneity of treatment effects across the categories of pre‐specified subgroup variables. Detailed statistical analyzes will be described in the statistical analysis plan. The trial results will be reported following the CONSORT guidelines for reporting randomized trials.

**Table 2 clc70049-tbl-0002:** List of covariates used in the covariate adjustment analysis.

Characteristics	Categories
Age	< 60, ≥ 60 year
Gender	Male, Female
Body mass index	< 28, ≥ 28 kg/m^2^
Diabetes	Yes, No
Hypertension	Yes, No
Hyperlipidemia	Yes, No
History of smoke	Yes, No
History of alcohol	Yes, No

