## Results

3

The first patient was enrolled on October 28, 2020. By April 2024, 9127 participants had been screened for the study, with 877 deemed ineligible, leading to the enrollment of 8250 patients (Figure 2). The mean age of the enrolled patients was 60.5 ± 8.8 years, with 5753 (69.7%) being men (Table 3).

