**Figure 2 clc70049-fig-0002:**
[figure not shown]
Monthly and cumulative recruitment.

**Table 3 clc70049-tbl-0003:** Preliminary data for patients enrolled as of April 2024.

Characteristics	*N* = 8250
Age, years	60.5 ± 8.8
Male gender, *n* (%)	5753 (69.7%)
Height, cm	168.0 ± 7.3
Weight, kg	71.6 ± 10.3
History of myocardial infarction, *n* (%)	2806 (34.0%)
History of heart failure, *n* (%)	732 (8.9%)
Systolic blood pressure, mmHg	131.4 ± 13.5
Diastolic blood pressure, mmHg	80.2 ± 9.4
History of hypertension, *n* (%)	4414 (53.5%)
History of diabetes, *n* (%)	2323 (28.2%)
Time since most recent PCI, day	378.6 ± 19.8

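### Table 2 splits age and BMI in two and leaves out prior MI and heart failure, so the supportive adjusted Cox analysis gives up a little recorded prognostic information for no saving

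*Protocol article*

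**What the plan says.** Section 2.7 (Statistical Considerations) first describes the primary comparison: Kaplan-Meier curves, a log-rank test and a Cox hazard ratio, with no covariates mentioned. It then adds a second, adjusted analysis: "Covariate adjustment analysis aims to control for possible imbalances in the covariates, as listed in Table 2". The model is named: "The Cox model will be used for the covariate‐adjusted analysis".

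Table 2, captioned "List of covariates used in the covariate adjustment analysis", gives eight covariates, each with two categories: age (cut at 60 years), gender, BMI (cut at 28 kg/m²), diabetes, hypertension, hyperlipidemia, smoking history and alcohol history. It gives no reason for the cuts or for the choice of variables.

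Table 3 (Section 3) shows what is recorded for the 8250 enrolled patients. Age, height and weight are continuous measurements. "History of myocardial infarction" is present in 2806 patients (34.0%), and heart failure in 732 (8.9%).

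Section 2.3 allocates patients 1:1 "using a completely random method" and describes no stratification.

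**The concern.** Controlling imbalance is the stated purpose of the adjusted analysis. A Cox model can do that only for the variables it contains, and only as finely as they are coded. Prior MI and heart failure are plausible predictors of cardiovascular death, MI and stroke, and MI is itself a component of the primary endpoint. Both are absent, while alcohol history is included. Age, another plausible predictor, is reduced to a near-median split.

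Two things are at stake. The adjusted hazard ratio retains whatever imbalance arises in the omitted factors and within the broad age and BMI bands. It also loses some power that the recorded data could supply. If an imbalance in prior MI appeared and the variable were added only then, the result would be post hoc, which is unwelcome in an open-label trial.

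**Working it through.** **1. The plan's own figure.** Section 2.6 gives 8250 patients for a hazard ratio of 0.8, two-sided 5% level and 80% power, with "the expected annual rate of MACCEs is estimated to be 5% in the control arm".

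- Events (Schoenfeld): 4(1.960 + 0.842)²/(ln 0.8)² = 631.
- Event probability: hazards of 0.05 and 0.04 per year, 2-year uniform accrual and 1-year minimum follow-up give 9.48% and 7.66%, mean 8.57%.
- N = 631/0.0857 ≈ 7362. Dividing by 0.95 for dropout gives 7749; dividing by 0.97² for switching gives 8236.

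This is close to 8250. The sample size is not in dispute; it sets the scale for step 5.

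**2. Information kept by the age split.** Section 3 states: "The mean age of the enrolled patients was 60.5 ± 8.8 years". For a normal covariate cut at z, the share of variance kept is φ(z)²/[p(1−p)].

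- z = (60 − 60.5)/8.8 = −0.057, and the proportion at or above 60 is p = 0.523.
- Share kept = 0.3983²/(0.523 × 0.477) ≈ 0.64. Truncating age at 75 gives 0.66.

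**3. Information kept by the BMI split.** The documents give no BMI distribution, so BMI was simulated from Table 3 (height 168.0 ± 7.3 cm, weight 71.6 ± 10.3 kg). The height-weight correlation is an assumption.

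| Correlation | BMI mean | BMI SD | At or above 28 | Share kept |
|---|---|---|---|---|
| 0 | 25.5 | 4.3 | 27% | 58% |
| 0.3 | 25.4 | 3.7 | 24% | 54% |
| 0.5 | 25.4 | 3.2 | 20% | 50% |
| 0.6 | 25.3 | 2.9 | 18% | 46% |

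**4. Chance imbalance in the omitted factors.** With 4125 per arm, the standard error of the between-arm difference is √[2p(1−p)/4125].

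- Prior MI: √(2 × 0.34 × 0.66/4125) = 0.0104; × 1.96 gives ±2.0 points.
- Heart failure: √(2 × 0.089 × 0.911/4125) = 0.0063; × 1.96 gives ±1.2 points.

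The unadjusted hazard ratio moves by roughly d(HR − 1)/[1 + p(HR − 1)] for an imbalance d. At the edges of those ranges:

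- Prior MI, assumed HR 1.5-1.8: 0.0204 × 0.5/1.17 = 0.9% to 0.0204 × 0.8/1.272 = 1.3%.
- Heart failure, assumed HR 1.8-2.2: 0.0123 × 0.8/1.071 = 0.9% to 0.0123 × 1.2/1.107 = 1.3%.

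Each is under one fifth of a standard error of 0.076.

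**5. Effect on the adjusted test.** Cox models were simulated with 8250 patients, 400 trials per scenario and a true hazard ratio of 0.8. Assumed throughout: diabetes HR 1.4, BMI HR 1.1 per 5 kg/m², height-weight correlation 0.5, and no dropout or switching. Model A used Table 2's coding of age, BMI and diabetes. Model B used continuous age and BMI, diabetes, prior MI and heart failure. The other five Table 2 covariates were given no effect and left out of both models.

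| Assumed HR: age per 10 y / MI / HF | Mean events | SE, A and B | Mean log HR, A → B | SD of A − B | Power, A → B |
|---|---|---|---|---|---|
| 1.2 / 1.3 / 1.5 | 704 | 0.0759, 0.0759 | −0.2251 → −0.2260 | 0.005 | 84.2% → 84.5% |
| 1.5 / 1.5 / 2.0 | 699 | 0.0762, 0.0762 | −0.2229 → −0.2243 | 0.009 | 83.2% → 83.6% |
| 2.0 / 2.0 / 2.5 | 685 | 0.0769, 0.0770 | −0.2179 → −0.2221 | 0.016 | 80.7% → 82.2% |

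Power is a normal approximation from the mean test statistic. The raw rejection rates (83.5% for both models, 83.3% for both, and 78.5% against 79.5%) are too coarse with 400 trials to resolve gains of this size. The standard error does not shrink. The gain comes from the adjusted log hazard ratio moving slightly away from zero.

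**The case against.** The strongest reply is that nothing important depends on this model. The primary comparison is unadjusted, and no sample-size, error-rate or decision rule uses the adjusted hazard ratio. That stands, and it limits the point to a minor one.

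Because randomisation is unstratified, a reader might infer that the adjusted model is the only safeguard against imbalance. The documents do not support that. Randomising about 4125 patients per arm is the main protection, and the unadjusted test and interval already allow for chance imbalance. The analysis plan and Supporting Information Appendix 1 are not shown and may contain further models.

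A reader might also infer that better covariates would narrow the confidence interval. In a Cox model they generally do not, as step 5 shows. Adding prognostic covariates also changes the quantity estimated, from a marginal to a more conditional hazard ratio.

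Nor does the source of the 5% event rate, a trial that the Introduction describes as enrolling patients with prior MI and multivessel disease, show that the covariate list is wrong. That bears on the event-rate assumption.

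Finally, the article defers detail to the statistical analysis plan. This does not remove the point, because Table 2 itself states both the variables and their categories. Read literally, the sentence above Table 2 promises control only of the listed covariates, so there is no contradiction in the text. The question is whether the list is a good one.

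**Conclusion.** The point holds as a minor, free improvement to a supportive analysis. Table 2 discards about 36% of the linear information in age and 42-54% of that in BMI. It also leaves the adjusted model unable to correct imbalance in two recorded, plausibly prognostic factors.

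The cost is about 0.3-1.4 points of power for the adjusted test, and a within-trial shift in the log hazard ratio with an SD of 0.005-0.016 against a standard error of about 0.076. That is unlikely to change a conclusion, and the primary analysis is untouched.

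The reading of Tables 2 and 3 is firm, and so are the age and imbalance figures, given a roughly normal age distribution and simple randomisation. The power and shift figures rest on assumed prognostic hazard ratios, because the documents give none. The BMI range rests on the assumed height-weight correlation.

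**What to change.** In Table 2, enter age and BMI as continuous terms (linear, or a spline with its form stated in advance), and add history of myocardial infarction and history of heart failure. Keep the cuts at 60 years and 28 kg/m² for subgroup display only. Fix the revised list, and carry it into the statistical analysis plan, before anyone sees outcomes by arm.

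The cost is an edit to one table and one model statement. It needs no new data or patients and no change to the primary analysis.
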